### 1476 3.5 Intervention being tested

1477 ViPP-SD is a home-based intervention, delivered over six sessions at approximately fortnightly intervals, which  
1478 shows high levels of parental acceptability. Each session involves filming parent-child interactions and giving  
1479 parents feedback based on these video clips.

1480 The intervention will be delivered by trained, supervised health professionals, predominantly health visitors.  
1481 They will deliver the intervention in research participants' homes (or another location according to participant  
1482 preference). The key role of the therapists will be to develop a trusting relationship with the participants in the  
1483 treatment arm, and to deliver the treatment in 6 sessions in accordance with the manual. They will be  
1484 supervised, and the treatment will be monitored closely for fidelity to the manual by the clinical supervisor (and  
1485 a proportion will be taped and assessed by an independent researcher trained in the intervention).

- 1486 • Four core sessions: these aim to enhance the parent's capacity to identify the child's exploratory behaviour  
1487 and attachment cues and to respond to them appropriately
- 1488 • Two booster sessions: these are spaced one month apart, and the key messages are repeated using continuing  
1489 video interaction material at each session

1490 Therapists responsible for delivering the intervention will be trained by the developers of ViPP-SD and will  
1491 undertake supervised clinical practice before becoming a therapist on the trial.

1492

1493 Participants in both groups will continue to receive their usual care. Usual care may include a range of services  
1494 such as the following:

- 1495 • health visitor services
- 1496 • GP advice
- 1497 • early intervention mental health services linked to children's centres
- 1498 • parenting advice and support sessions

1499 Data on concurrent use of health services will be collected including number of sessions offered, where they  
1500 were provided, and which healthcare (or other non-healthcare) professionals provided the care.

1501

### 1502 3.6 Sample Size

1503 The total sample size will be 300 participants.

1504 If losses to follow-up are 20%, this leaves 120 participants per group with follow-up data. We would then have  
1505 80% and 90% power to detect standardised effect sizes of 0.36 and 0.42 respectively, at the 5% significance  
1506 level, using an independent samples t-test. In addition, we have stated that our analysis will adjust for baseline  
1507 behavioural score, research centre and age of child, and parental involvement (one versus two) which will  
1508 increase power, probably to over 90% for the 0.36 effect size (since such adjustment will reduce the residual  
1509 error variance in our model). Kahan and colleagues (2014, ref 1) found that covariate adjustment for 1 to 4  
1510 variables in trials increased power from 80% to a median of 93% power in their sample of 12 outcomes assessed  
1511 across 8 studies.)

1512 We have conservatively allowed for a potential drop-out rate of 20% because of the longer follow-up time in the  
1513 proposed study, even though previous intervention studies detailed below have maintained retention rates of  
1514 over 90% at follow-up.

1515 The pooled effect size for all randomised controlled trials to date that have used the same video feedback  
1516 intervention (ViPP) is 0.46 ([name], 2013, personal correspondence). Other relevant literature  
1517 for interventions for behavioural problems, predominantly in slightly older children, yield higher effect size  
1518 estimates. In the systematic reviews undertaken for the most recent NICE guidance on conduct disorders in  
1519 children and young people (ref 2), the pooled effects for parent-focussed interventions yielded estimated effect  
1520 sizes of 0.69 standard deviations for researcher-rated outcome (the main outcome measure in the proposed  
1521 study), and 0.54 for parent-rated outcome. In a study of the Incredible Years programme in 2-9 year olds (ref 3)  
1522 effect sizes ranged from 0.48-0.78. In the SPOKES trial (ref 4) of intervention for parents of 6 year olds, the  
1523 effect size for behavioural outcomes was 0.52 SD difference between the treatment and control group. Where  
1524 parenting programmes have been rolled out across the UK (ref 5-6) similar effect sizes have been found, albeit  
1525 in non-randomised designs (effect sizes ranged from 0.44-0.71).

1526

1527 **Change from official signed draft:** the statement of sample size calculation (**section 3.6 Sample Size**) was  
1528 changed to clarify that this was based on a t-test.

|  | Baseline | 5 month f/u | 24 month f/u |
|--|----------|-------------|--------------|
|--|----------|-------------|--------------|

1529  
1530 **3.7 Schedule of Time and Events**

1531 The study funding began on 1 October 2014, with recruitment commencing in June 2015. Recruitment finished  
1532 in July 2017. All children will be followed up for two years from date of randomisation.

1533  
1534 **3.8 ViPP-SD Visit Schedule**

|                | ViPP Intervention Schedule a            |                                     |                                     |                                     |                                     |                                     |
|----------------|----------------------------------------------------|-------------------------------------|-------------------------------------|-------------------------------------|-------------------------------------|-------------------------------------|
| Visit          | 1                                                  | 2                                   | 3                                   | 4                                   | 5                                   | 6                                   |
| Day/Week/Month | Day 14-28
(+/- 7 days)
post
randomisation | Visit 1 plus
14 days
(+/-7 d) | Visit 2 plus
14 days
(+/-7 d) | Visit 3 plus
14 days
(+/-7 d) | Visit 4 plus
21 days
(+/-7 d) | Visit 5 plus
21 days (+/-7
d) |

1535 *Note. aVisit schedule is a guide for optimal treatment delivery, variation is expected given the pragmatic context of the trial.*

1536  
1537 **3.9 Figure 1. Assessment schedule**

| Visit                                                                | 1 | 7                                           | 8                                            |
|----------------------------------------------------------------------|---|---------------------------------------------|----------------------------------------------|
| Day/Week/Month                                                       |   | Month 5 post randomisation
(+/- 3 weeks) | Month 24 post randomisation
(+/- 2 weeks) |
| Informed consent                                                     | X |                                             |                                              |
| Inclusion & exclusion criteria                                       | X |                                             |                                              |
| Demographics and medical history                                     | X |                                             |                                              |
| AUDIT-C                                                              | X | X                                           |                                              |
| Randomisation                                                        | X |                                             |                                              |
| CBCL on child assessed by -
parent/care-giver 1                   | X | X                                           | X                                            |
| CBCL on child assessed by -
parent/care-giver 2                   | X | X                                           | X                                            |
| SDQ on child assessed by -
parent/care-giver 1                    | X | X                                           | X                                            |
| SDQ on child assessed by -
parent/care-giver 2                    | X | X                                           | X                                            |
| SDQ on child – assessed by teacher/
care-giver outside the family |   |                                             | X                                            |
| GAD-7 - parent/care-giver 1                                          | X | X                                           | X                                            |
| GAD-7 - parent/care-giver 2                                          | X | X                                           | X                                            |
| PPACS interview on child                                             | X | X                                           | X                                            |
| PHQ-9 – parent/care-giver 1                                          | X | X                                           | X                                            |
| PHQ-9 – parent/care-giver 2                                          | X | X                                           | X                                            |
| Revised Dyadic Adjustment Scale -
parent/care-giver 1             | X | X                                           | X                                            |
| Revised Dyadic Adjustment Scale -
parent/care-giver 2             | X | X                                           | X                                            |
| Parenting Scale - parent/care-giver 1                                | X | X                                           | X                                            |
| Parenting Scale - parent/care-giver 2                                | X | X                                           | X                                            |
| CA-SUS                                                               | X | X                                           | X                                            |
| Parent-Child interactions collection of
videos                    | X | X                                           | X                                            |
| Feedback questionnaire                                               |   | X                                           |                                              |
| Serious adverse events                                               | X | X                                           | X                                            |

Note that not all families have a participating secondary care-giver, so data on second care-giver will not always be available.

### 3.10 Randomisation

Randomisation lists were prepared by a statistician independent of the trial ([name]) using computer generated 1:1 allocation (ViPP intervention vs treatment as usual) and variable block sizes. Randomisation will be stratified by treatment centre and by number of parents/ care-givers participating (one or two). The randomisation lists (one for each strata) will be uploaded on to InForm (the study electronic data capture system) and eligible subjects allocated online to the next available treatment code in the appropriate randomisation list.

## 1548 4 Randomised populations

### 1549 4.1 Intent-to-Treat Population

1550 The primary analysis will be conducted using intention to treat approach. A substantial effort will be made to  
1551 obtain follow-up data on all participants (unless they drop out of the study and withdraw their consent to our  
1552 following them up). Baseline data will be analysed on all patients, unless they withdraw consent for this data to  
1553 be used.

### 1554 1555 4.2 Safety population

1556 The safety population will be children and their parents/ care-givers who have received at least one intervention  
1557 as part of the ViPP programme, compared to those allocated to the control group who have not received any  
1558 ViPP intervention. Adverse events will be compared between arms according to these safety definitions of  
1559 groups.

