| Visit          | 1                                         | 2                              | 3                              | 4                              | 5                              | 6                              |
| Day/Week/Month | Day 14-28 (+/- 7 days) post randomisation | Visit 1 plus 14 days (+/- 7 d) | Visit 2 plus 14 days (+/- 7 d) | Visit 3 plus 14 days (+/- 7 d) | Visit 4 plus 21 days (+/- 7 d) | Visit 5 plus 21 days (+/- 7 d) |

546 *Note. aVisit schedule is a guide for optimal treatment delivery, variation is expected*

547 *given the pragmatic context of the trial.*

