## 1260 **eDocument 2. Pre-specified statistical analysis plan**

### 1261 **Additional details for statistical policies**

1262 Continuous/numeric variables that follow an approximately normal distribution are summarised using the mean  
1263 and standard deviations. Skewed variables are summarised using the median and inter-quartile range.  
1264 Categorical variables are presented as frequencies and percentages. Scores from psychometric scales are treated  
1265 as numeric. Histograms and box-plots are used to assess distributional assumptions and to check for possible  
1266 outliers. The significance level for statistical tests is set at 5%. The primary analysis was conducted on an  
1267 intention to treat basis. The safety population comprises children and their parents/ caregivers who had received  
1268 at least one intervention session as part of the VIPP-SD programme plus those allocated to the usual care group  
1269 who did not receive any VIPP intervention. All analyses (unless indicated otherwise) were undertaken using  
1270 Stata version 13 and 15 following a pre-specified statistical analysis plan.

1271

1272

1273

1274

1275

**Statistical Analysis Plan (SAP) version 2.0  
for Healthy Start, Happy Start**  
Based on protocol version 6.0

Principal Investigator: [name]

Study Investigators (alphabetically):  
[name]  
[name]  
[name]  
[name]  
[name]  
[name]  
[name]

Study Management Team: [name] and [name]

SAP Working Group: [name] and [name] ([name] and [name] for the economics section)

| Version | Date       | Lead Author |
|---------|------------|-------------|
| 2.0     | 7 May 2019 | [name] |

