### 1614 5.3 Safety Variables

1615 There are no obvious adverse events that are expected to be related to the ViPP intervention and the risk to  
1616 participants is believed to be low. We have therefore not specified any particular type of adverse events in  
1617 advance, other than serious adverse events, for routine collection. Information on all serious adverse events  
1618 affecting any family members who are participating in the study (i.e. the child and the one or two participating  
1619 care-givers) will be collected for the duration of the follow-up period, irrespective of the likely connection to the  
1620 intervention. Information on mild to moderate adverse events will be collected only if the event might plausibly  
1621 be attributable to the intervention.

1622 It is important to note that some adverse events (such as incarceration or death of sibling) may be reported  
1623 indirectly, through the process of re-scheduling appointments, for example, rather than directly as an adverse  
1624 event. The database notes columns will be scrutinised prior to analysis in order to identify these. Hospitalisation  
1625 of the child, will be collected via the CASUS form which is designed to collect health care utilisation data for  
1626 the economic analysis.

1627

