## 1792 6.5 Safety Analysis

1793 A table of serious adverse events and any adverse events considered to be relevant will be produced, by type of  
1794 event and by treatment received.

1795 The table will show numbers of children who have at least one such adverse event of a given type and then  
1796 numbers of families where at least one parent/care-giver is affected by this type of adverse event. Percentages  
1797 (of children/ families) will be calculated and presented. Proportions will be compared between treatment groups  
1798 using Fisher's exact test.

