| Elements of intervention completed (%):                                             |                  |            |            |            |           |  |  |  |  |  |
| Speak for child                                                                     |                  |            |            |            |           |  |  |  |  |  |
| Attachment messages                                                                 |                  |            |            |            |           |  |  |  |  |  |
| Set Message                                                                         |                  |            |            |            |           |  |  |  |  |  |
| Set Explanation                                                                     |                  |            |            |            |           |  |  |  |  |  |
| Exploration of messages                                                             |                  |            |            |            |           |  |  |  |  |  |
| Duration of video recording: Mean (SD)                                              |                  |            |            |            |           |  |  |  |  |  |
| Duration of visit, therapist reported: Mean (SD)                                    |                  |            |            |            |           |  |  |  |  |  |

1957

1958

1959

1960

1961

1962 8.17 Table: Adverse Events

|                                                                                                     | Received ViPP (at
least one appointment) | Allocated to control
group (and did not
receive any
appointments for ViPP) |                                                                             |
|-----------------------------------------------------------------------------------------------------|---------------------------------------------|-------------------------------------------------------------------------------------|-----------------------------------------------------------------------------|
|                                                                                                     | (n=number of
families)                   | (n=number of families)                                                              | p-value by
Fisher's exact
test for
difference
between
groups |

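### The only between-group safety comparison omits ViPP-allocated families who never start but has no matching exclusion for controls; it can make ViPP look safer, though the net direction and size of bias are unknown

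*Combined protocol and SAP*

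**What the plan says.** SAP 4.2 sets the two safety groups. The first is defined by receipt: "The safety population will be children and their parents/ care-givers who have received at least one intervention". The text goes on: "as part of the ViPP programme, compared to those allocated to the control group who have not received any" ViPP. It then makes these the comparison groups: "Adverse events will be compared between arms according to these safety definitions of" groups. The policy text at the head of eDocument 2 repeats the definition: "at least one intervention session as part of the VIPP-SD programme plus those allocated to the usual care group" who had no ViPP.

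SAP 6.5 tabulates by type of "event and by treatment received" and compares proportions with Fisher's exact test. Table 8.17 has two group columns. One is headed "Received ViPP (at least one appointment"); the other is for controls with no ViPP appointment.

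Three other places matter:

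- **SAP 5.3.** SAEs in participating family members (the child and the one or two "care-givers) will be collected for the duration of the follow-up period, irrespective of the likely connection to the" intervention) are recorded whether or not the family was treated.
- **Protocol 11.7 and SAP 3.8.** The first session is planned for "Day 14-28 (+/- 7 days) post randomisation". A note calls the schedule a guide and expects variation.
- **SAP Table 8.13.** It counts ViPP-allocated families by number of sessions, including zero, but does not report their events.

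**The concern.** A ViPP-allocated family with no session fits neither definition, so the family and all its events over 24 months drop out of the comparison. Usual care has no start to fail, so the control families who would have behaved in the same way stay in. This is not a full as-treated analysis either, since that would move untreated ViPP families to the untreated column rather than omit them.

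The plan itself links adverse events to attendance. Protocol 9.2 lists health compromised by adverse events or illness as a reason to stop the intervention or withdraw. SAP 5.3 expects some events to come to light when appointments are rearranged. Where an event permanently prevents the first session, it can be removed only from the ViPP side.

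At stake is the only formal between-group safety test. Efficacy is analysed by intention to treat (SAP 4.1). Safety loses the protection of randomisation although the data to keep it are already being collected.

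**Working it through.** **Inputs.** The documents give 150 families per arm (Protocol 6, SAP 3.3), two years of follow-up (SAP 3.7) and a first session between day 14 - 7 = 7 and day 28 + 7 = 35 (Protocol 11.7). They give no SAE risk, no non-start rate and no safety power figure, so there is no figure of the plan's own to reproduce. The values of p, f and k below are assumptions.

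**Step 1: who is counted.**

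| Allocated to | Sessions received | Place in Table 8.17 |
|---|---|---|
| ViPP | 1 or more | ViPP column |
| ViPP | 0 | neither column |
| Control | 0 | control column |
| Control | 1 or more (off protocol) | meets the ViPP definition |

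**Step 2: expected ratio under no true effect.** Let both arms have true risk p. A fraction f of ViPP families never start, with k times the starters' risk r. Then p = (1 - f)r + fkr. The ViPP column shows r and the control column shows p, so the shown risk ratio is r/p = 1/(1 - f + fk).

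| f | k | 1 - f + fk | Shown ratio |
|---|---|---|---|
| 10% | 0.5 | 0.95 | 1.05 |
| 20% | 0.5 | 0.90 | 1.11 |
| any | 1 | 1.00 | 1.00 |
| 5% | 2 | 1.05 | 0.95 |
| 10% | 2 | 1.10 | 0.91 |
| 10% | 3 | 1.20 | 0.83 |
| 20% | 3 | 1.40 | 0.71 |

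If all families are analysed as randomised, the expected ratio is 1.00 in every row.

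**Step 3: one case in counts.** Take p = 10%, f = 10% and k = 3.

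- Starters' risk is 0.10/1.20 = 8.33%, so 135 x 0.0833 = 11.25 families with an event are shown.
- Non-starters' risk is 3 x 8.33% = 25%, so 15 x 0.25 = 3.75 are omitted.
- The table shows 11.25/135 = 8.3% against 15/150 = 10%.

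In whole numbers, suppose each arm truly has 15/150 and there are 15 non-starters. If they hold 3 events, the table shows 12/135 = 8.9% against 10.0% (Fisher p = 0.84). If they hold none, it shows 15/135 = 11.1%, and ViPP looks less safe.

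**Step 4: pre-start events alone.** Assume a constant hazard, and that every family with an event before its first-session date never starts. The window is 7 to 35 of about 730 days, or 1% to 5% of follow-up. For a 35-day window and p = 10%, the proportion lost is q = 1 - 0.9^(35/730.5) = 0.5%, or 0.76 of 150 families. The shown risk is (0.10 - q)/(1 - q) = 9.54%, a ratio of 0.95. Over windows of 7 to 35 days and p = 5% to 20%, 0.07 to 1.6 families are lost and the ratio is 0.95 to 0.99. Ratios such as 0.83 therefore need non-starters to carry a higher risk throughout the 24 months.

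**The case against.** A reader might infer that the table is bound to flatter ViPP. The documents do not support that. The ratio is 1.00 when non-starters and starters have equal risk, and it exceeds 1 when non-starters have fewer events. Nothing in the documents says that families who fail to start have more SAEs later. Other forces may push the other way: control families who obtain ViPP carry their events into the ViPP column, and up to six extra appointments give more occasions for events in that arm to surface. All of this stands. It limits the claim about direction but does not restore the comparison.

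A family that starts late keeps its pre-start events, because SAP 4.2 sets no on-treatment window. Only permanent non-start removes them. That stands too, and it is a further reason to expect the pre-start effect to be small.

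Nor do the events vanish from the trial. Every SAE is to be reported and reviewed by the Chief Investigator (Protocol 12.4.2), and the data monitoring committee reviews SAE reports (Protocol 17.7). The loss is confined to the comparison.

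Finally, a population with at least one session is a defensible choice for harm caused by delivered sessions. If sessions double the risk (R = 2) with f = 10% and k = 1, the existing comparison shows 2.00, while analysis by allocation shows 0.9 x 2 + 0.1 x 1 = 1.90. The existing comparison shows the larger excess whenever k is below R. This is a good reason to keep it, but not to have it alone. Analysis by allocation is not perfect either, since it cannot repair withdrawal from follow-up or unequal ascertainment.

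**Conclusion.** The point holds in a limited form. SAP 4.2, SAP 6.5, Table 8.17 and the eDocument 2 policy text agree in omitting ViPP-allocated non-starters while keeping their control counterparts, and nothing else in the plan compares safety by randomised group. The comparison can therefore be biased, and an event that itself permanently prevents starting can act only in ViPP's favour.

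The net direction and size cannot be determined from the documents. Under the assumed values of f and k above, the expected ratio with no true effect runs from 0.71 to 1.11. The pre-start mechanism alone gives about 0.95 to 0.99 on the planned schedule. The stronger conclusion, that ViPP will look safer than it is, needs k above 1 and no offset from control crossovers or ascertainment, and the documents establish neither. The change is still worth making, because it removes the dependence on f and k using data already collected.

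**What to change.** In SAP 4.2, 6.5 and Table 8.17, and in the eDocument 2 policy text, add a safety comparison of all randomised families by allocated group, with events counted from the date of randomisation. List separately the SAEs in ViPP-allocated families who had no session. Keep the existing at-least-one-session comparison alongside, labelled as by treatment received, since it is less diluted for harm from delivered sessions. State in its footnote how many ViPP-allocated families are in neither column and how many control families have moved to the ViPP column.

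The cost is some SAP wording and one additional table. No new data are needed, because SAP 5.3 already collects SAEs on all participating family members throughout follow-up.
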